### Sample size

Sample-size calculation was performed to determine the number of classes needed in order to be able to detect a difference between the intervention and comparison group with respect to student well-being, smoking and school dropout [46]. From a nationwide student satisfaction survey in 2010 at Danish vocational schools, we selected measures on daily smoking (yes, no), consideration of dropping out (yes, no), and two indicators on student well-being: solidarity among students (yes, no), and a positive welcoming atmosphere created by the school (yes, no). Overall, 41 % were daily smokers, 19 % considered dropping out, 17 % reported a lack of student solidarity, and 21 % reported a lack of a positive welcoming atmosphere. We estimated the intra-class correlation to 0.006 for welcoming atmosphere, 0.05 for student solidarity and smoking, and 0.016 for dropout considerations. With a desired power of 80 %, a 5 % significance level, a two-sided test, and an expected 20 % reduction for each outcome in the intervention group, the minimum number of classes in intervention and comparison groups was calculated as ranging from 60 to 110. To be conservative, we chose the highest number of clusters (i.e., classes, *n* = 110). Another necessary assumption for the power calculation was that each class had an average of 20 students. Allowing for 20 % non-respondents, a total of about 5,280 students needed to be included.

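### On the plan's own inputs student solidarity needs about 171 to 177 classes per group, so 110 is not the maximum and gives that indicator about 61% power, not 80%

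*Protocol article*

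**What the plan says.** The Sample size section of the protocol article plans on four yes/no measures from a 2010 national survey. The rates are "41 % were daily smokers, 19 % considered dropping out, 17 % reported a lack of student solidarity", and "21 % reported a lack of a positive welcoming atmosphere". The intra-class correlations are 0.006 for welcoming atmosphere and "0.05 for student solidarity and smoking, and 0.016 for dropout considerations". The design targets are "With a desired power of 80 %, a 5 % significance level, a two-sided test" and "an expected 20 % reduction for each outcome in the intervention group", with an average of 20 students per class.

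From these, "the minimum number of classes in intervention and comparison groups was calculated as ranging from 60 to 110". The section then says "To be conservative, we chose the highest number of clusters", which is 110, and arrives at about 5,280 students after allowing for 20% non-response.

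**The concern.** Solidarity has the lowest rate of the four measures and shares the highest intra-class correlation. With the same relative reduction, power and class size for all four, it must need the most classes. A maximum of 110 looked too small for it.

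The Outcome measures section makes student well-being a primary outcome, and the sample size is presented as sufficient to detect a difference in it. Solidarity is one of only two planning indicators for that outcome. If 110 is not the true maximum, a null well-being result would be read as coming from a study with at least 80% power when the printed inputs do not support that. Later trials could also reuse a wrong intra-class correlation or class count.

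**Working it through.** **Inputs (all from the Sample size section).** Two-sided 5% and 80% power, so (1.960 + 0.842)² = 7.849. Class size m = 20. The 20% reduction must be relative (p₂ = 0.8 p₁), because a 20-point absolute fall is impossible from 17% or 19%.

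**Is 110 per group?** 110 × 2 × 20 × 1.2 = 5,280, the stated total. So 110 is per group, and 20 is the number of responding students per class.

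**Formula.** n per group = 7.849 × [p₁(1−p₁) + p₂(1−p₂)] / (p₁−p₂)². The design effect is DE = 1 + 19 × ICC. Classes per group = n × DE / 20.

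**Solidarity.**
- p₁ = 0.17, p₂ = 0.136, difference 0.034
- Variance term: 0.1411 + 0.1175 = 0.2586
- n = 7.849 × 0.2586 / 0.001156 = 1,756
- DE = 1 + 19 × 0.05 = 1.95
- Students per group: 1,756 × 1.95 = 3,424
- Classes per group: 3,424 / 20 = 171.2

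The pooled-variance version gives 1,759 and 171.5 classes. With continuity correction it gives 1,817 and 177.2 classes (3,543 students).

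**All four measures at m = 20.** The ranges run from unpooled to continuity-corrected. Power is for 110 classes of 20 per group.

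| Measure | Rate | ICC | DE | n per group, no clustering | Classes per group | Power at 110 |
|---|---|---|---|---|---|---|
| Smoking | 41% | 0.05 | 1.95 | 540–567 | 52.6–55.3 | 98% |
| Welcoming atmosphere | 21% | 0.006 | 1.114 | 1,360–1,411 | 75.8–78.6 | 92% |
| Dropout considerations | 19% | 0.016 | 1.304 | 1,537–1,593 | 100.2–103.9 | 83% |
| Solidarity | 17% | 0.05 | 1.95 | 1,756–1,817 | 171.2–177.2 | 61% |

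The stated 60 to 110 is not reproduced exactly. The first three measures give about 53 to 104, which is close. Solidarity lies far outside.

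**A check that depends little on the formula.** The stated maximum over the stated minimum is 110 / 60 = 1.83. Dropout considerations over smoking is 100.2 / 52.6 = 1.90. Solidarity over smoking is 171.2 / 52.6 = 3.25. The printed range behaves as if dropout considerations were the largest requirement and solidarity had been left out or entered with a smaller ICC.

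**Power for solidarity at 110 classes.** Effective n per group = 2,200 / 1.95 = 1,128. The standard error is √(0.2586 / 1,128) = 0.01514. Then 0.034 / 0.01514 = 2.246, less 1.960 leaves 0.286, which is a power of 61%.

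**Detectable reduction for solidarity.** With the same effective n, 80% power is reached at p₂ = 0.128, a relative reduction of about 25%.

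**Other formulas for solidarity.** Arcsine gives 171.1 classes, the Hayes-Bennett cluster formula 167.4, and the control-rate variance in both groups 186.8. A one-sided test, contrary to the text, gives 135.1. Class sizes of 16, 24 and 25 give 192.4, 157.6 and 154.8. None reaches 110. Without any clustering, solidarity already needs 88.

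**Would a misprinted ICC explain it?** On the pooled formula solidarity reaches 110 at an ICC of about 0.013: (2,200 / 1,759 − 1) / 19. At 0.005 it needs about 96 classes. The text gives one shared value for solidarity and smoking, however, and at 0.005 smoking would fall to about 30 classes, well below the stated minimum of 60. A misprint therefore works only if it affects solidarity alone.

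**The case against.** The arithmetic is not seriously in dispute. The case on the other side is about how far it reaches.

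- **The 61% is conditional.** If the printed ICC for solidarity is the error, there is no power shortfall, only a misprint. This stands: what the article proves is a contradiction between its inputs and its maximum.
- **Solidarity is a planning proxy.** It is a single yes/no survey item, whereas the primary outcome is a set of multi-item scales with a four-factor structure still to be validated. The other well-being indicator, welcoming atmosphere, has about 92% power. This also stands: 61% is the power for the solidarity indicator, not for the final well-being analysis. Solidarity is nevertheless the closer proxy, since peer relations are part of the well-being definition, while feeling welcome on the first day is listed among the immediate impacts.
- **Recruitment is over.** Precision will come from the achieved data. That is true and keeps the remedy small, but it does not make the printed sentence correct.
- **The authors' method is in a cited source that is not shown**, and neither 60 nor 110 is reproduced exactly. This cautions against treating one formula as definitive. It does not rescue the maximum, since two-sided variants at 20 per class all give about 167 to 187 classes for solidarity.
- **Rounding.** In whole classes, solidarity needs 172 to 178, not 171 to 177. This is correct and immaterial.

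**Conclusion.** The concern holds. On the printed inputs, 110 classes per group is neither the highest requirement nor a conservative choice. Solidarity needs about 171 to 177 classes, or about 3,420 to 3,540 students per group against 2,200 planned. At 110 classes its power is about 61% and its detectable reduction about 25%. The other three measures have at least 80% power.

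This rests on a relative 20% reduction, 20 responding students per class, equal groups (implied by the total of 5,280) and an ICC of 0.05 for solidarity as printed. If that ICC is wrong, the error lies there and not in the class number. Either way the section contradicts itself on a figure used to justify the sample size for a primary outcome.

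**What to change.** Go back to the original calculation and establish which figure is wrong.

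- **If the solidarity ICC was misreported:** correct it, state separately the value used for smoking, and confirm that the range then follows.
- **If 0.05 is right:** give the range as about 53 to 177 classes per group (53 to 178 in whole classes). State that 110 classes give at least 80% power for smoking, dropout considerations and welcoming atmosphere, and about 61% for solidarity, with a detectable reduction of about 25%. Remove the description of 110 as the highest and conservative number.

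The cost is a restatement of figures, with no further recruitment and no change to the outcomes or analysis. In the second case, the power claim for the solidarity indicator becomes less favourable.

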### Participant flow

In total, we included 32 college units of 10 large and diverse technical and agricultural vocational schools; a sample of approximately 22 % of all Danish technical and agricultural vocational schools. Figure 2 shows the flow of students through the recruitment and analysis phase. The baseline survey resulted in responses from 2,329 students from four intervention schools and 3,371 students from six comparison schools, representing 73 % and 81 %, respectively, of the students assumed to be eligible. The true rate is likely to be higher because, as is typical, a number of students never started, despite enrolment on the class list, and were thus not eligible for inclusion. The majority (95 % and 97 %, respectively) who were in school on the day of data collection did respond to the questionnaire. Forty-eight students were excluded because of two or more errors identified in the data control (e.g., they reported smoking ≥ 70 cigarettes per day). The response rates for the follow-up questionnaire survey were 58 % and 52 %, respectively. The response rates of reporting the personal identification number (necessary for linkage with the education register to obtain dropout at the second follow-up) were 91 % and 88 %, respectively.

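### The target of about 5,280 students adds 20% to the 4,400 needed instead of dividing by 0.8; the stated allowance requires 5,500

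*Protocol article*

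**What the plan says.** The Sample size section of the protocol article sets the error rates ("With a desired power of 80 %, a 5 % significance level, a two-sided test") and the effect ("an expected 20 % reduction for each outcome in the intervention group"). It takes control rates from a national student survey ("41 % were daily smokers, 19 % considered dropping out, 17 % reported a lack of student solidarity, and 21 % reported a lack of a positive") and gives intra-class correlations of "0.006 for welcoming atmosphere, 0.05 for student solidarity and smoking, and 0.016 for dropout considerations". The class numbers obtained range from 60 to 110, and the authors report that "we chose the highest number of clusters (i.e., classes, *n* = 110", the upper end, to be conservative. Class size is taken as 20 on average. After an allowance of 20% for non-respondents, the section states that "a total of about 5,280 students needed to be included".

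The Participant flow section reports 2,329 baseline respondents in intervention schools and 3,371 in comparison schools, put at 73% and 81% of the students assumed eligible. It continues: "The response rates for the follow-up questionnaire survey were" 58% and 52%. The personal identification number needed for register linkage was given by 91% and 88%. Table 1 places student well-being and smoking, two of the three primary outcomes, at the 10-week survey. The third, dropout, comes from registers at two years.

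**The concern.** An allowance for non-response has to leave the required number of responders once the expected fraction is lost. This means dividing the requirement by one minus that fraction. Adding the same fraction to the requirement always gives too small a total, and the stated 5,280 looks like that operation.

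At stake is whether the only student target in the article supports the power claimed beside it. A second question follows from the article's own results: the 20% allowance was not met at the 10-week survey, and no section returns to the power statement for the outcomes measured there.

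**Working it through.** **Inputs.** From Sample size: 110 classes, 20 students per class, 20% non-response, two-sided 5% level, 20% relative reduction, and the control rates and intra-class correlations quoted above. From Participant flow: 2,329 and 3,371 baseline respondents; baseline response 73% and 81%; 10-week response 58% and 52%; identification number 91% and 88%.

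**1. Reproducing the stated total.** The 110 classes must be per group.
- Responders required: 2 × 110 × 20 = 4,400.
- 4,400 × 1.2 = 5,280, the stated figure exactly.
- With 110 classes in total, the requirement is 2,200, and 2,200 × 1.2 = 2,640 or 2,200 / 0.8 = 2,750. Neither matches.

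**2. Testing it against its own allowance.**
- 5,280 × 0.8 = 4,224 responders, short by 4,400 − 4,224 = 176 (176 / 4,400 = 4.0%).
- Non-response that 5,280 can absorb: 1 − 4,400 / 5,280 = 16.7%.
- Total that meets the allowance: 4,400 / 0.8 = 5,500 (2,750 per group), which is 220 more.

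**3. Effect on power.** With m responders per class, the effective size per group is n = 110m / [1 + (m − 1) × ICC]. Power for p₁ against p₂ = 0.8p₁, with mean p̄, is Φ{[(p₁ − p₂)√n − 1.96√(2p̄(1 − p̄))] / √(p₁(1 − p₁) + p₂(1 − p₂))}. A total of 4,224 over 220 classes gives m = 19.2.

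Example, dropout considerations (p₁ = 0.19, ICC 0.016): at m = 20, n = 2,200 / 1.304 = 1,687 and power is 83.5%. At m = 19.2, n = 2,112 / 1.2912 = 1,636 and power is 82.3%.

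| Planning measure | 4,400 responders | 4,224 responders |
|---|---|---|
| Smoking | 98.1% | 97.9% |
| Welcoming atmosphere | 92.1% | 91.2% |
| Dropout considerations | 83.5% | 82.3% |
| Solidarity | 61.2% | 60.3% |

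The slip costs about one percentage point at most. Baseline respondents number 2,329 + 3,371 = 5,700, above 5,500.

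**4. The 10-week survey.** Non-response was 100 − 58 = 42% and 100 − 52 = 48%. The text does not give the base of these rates, and the flow figure is not shown, so both readings are taken.
- Base of baseline respondents: 0.58 × 2,329 + 0.52 × 3,371 = 1,351 + 1,753 = 3,104.
- Base of eligible students: 2,329 / 0.73 = 3,190 and 3,371 / 0.81 = 4,162. Then 0.58 × 3,190 + 0.52 × 4,162 = 1,850 + 2,164 = 4,014.

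Both are below 4,400. Power by the same formula, assuming 110 equal classes per group:

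| Planning measure | 4,400 | About 4,014 | About 3,104 |
|---|---|---|---|
| Smoking | 98% | 98% | 96% |
| Welcoming atmosphere | 92% | 90% | 82% |
| Solidarity | 61% | 59% | 53% |

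**5. Register-based dropout.** Missing identification numbers were 9% and 12%, both within 20%. If the base is baseline respondents, 0.91 × 2,329 + 0.88 × 3,371 = about 5,086 students can be linked, against 4,400.

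**The case against.** The strongest reply is that this changes nothing in practice. The figure is given as approximate, the gap is 4%, baseline data collection ended in October 2012 and the total enrolled passed even the corrected target. All of that stands, and it limits the point to a correction. It does not make 5,280 right: the number is the exact product of the wrong operation, so rounding does not explain it.

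It can also be said that a low follow-up response is a result, not a planning error. That stands too. The article reports the rates openly, acknowledges in Study strengths and limitations that dropout harmed retention, and in Evaluation methods provides for missing data and an analysis of loss to follow-up. The base of the rates may well be in the flow figure, so its absence from the text is not held against the article.

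A reader might go further in two ways that the documents do not support:
- **That the intervention arm was under-recruited**, because 2,329 is below 2,640 or 2,750. This sets students who had already responded against targets drawn up before non-response. Like for like, 2,329 respondents exceed the 2,200 needed (110 × 20), and about 3,190 eligible students exceed 2,750. A shortfall appears only if the 20% means follow-up loss alone, which the section does not say.
- **That the slip or the attrition explains low power for solidarity.** On the stated inputs, solidarity has only about 61% power with the full 110 classes of 20 per group and no loss at all. Most of its distance from 80% therefore comes from the number of classes, which is a separate matter.

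**Conclusion.** The stated total is wrong under the plan's own allowance: it should be 5,500, not about 5,280. This rests only on the section's own figures and on 110 classes per group, the one reading that reproduces 5,280. It is a minor error, with a shortfall of 176 responders and about one percentage point of power, and it did not leave the study short at baseline.

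The secondary point is one of interpretation. For the 10-week questionnaire outcomes the allowance was exceeded at least twofold, leaving about 3,104 to 4,014 responders against 4,400, so the planned power does not carry over unchanged. The power figures for that survey assume equal groups and 110 equal classes per group; the achieved number of classes is not in the text.

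It would be too strong to infer that the questionnaire outcomes as a whole are underpowered. Even at 3,104 responders, smoking keeps about 96% power and welcoming atmosphere about 82%. Register-based dropout lies within the allowance.

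**What to change.** In Sample size, replace about 5,280 with 5,500 (2,750 per group), show the step as 4,400 / 0.8, and note that the 5,700 baseline respondents exceeded it. Add one or two sentences saying that non-response at 10 weeks was 42% and 48% against the 20% allowed for, so the power statement does not apply unchanged to well-being and smoking at that survey, while register-based dropout is not affected. The cost is one corrected number and a short note; recruitment and analysis stay as they are.

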### Evaluation methods

Initially, we will conduct scale validation of the student well-being outcome measure, which we hypothesise to be a four-factor model. Intervention effects will be evaluated by multilevel regression methods, specifically, a multilevel regression analysis accounting for the hierarchical data structure with students nested within classes in which the intervention was implemented, and classes nested within college units. We will use mediation analyses to explore the extent to which any intervention effects are mediated by changes in the measured immediate intervention impacts. The analyses will be conducted for the total study population. The smoking analysis will be repeated whereby students are analyzed according to their baseline smoking status. Analysis of subgroups will be conducted defined by age, parental socioeconomic status and basic course. To assess the stability of the available case analyses, handling of missing data will be conducted and analysis of loss to follow-up will indicate which variables to include.

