**Methods/design:**

The evaluation employed a non-randomised cluster controlled design, and schools were selected to either implement the intervention or continue with normal practice for comparison. In the baseline survey conducted 2011–2012, 2,329 students from four intervention schools and 3,371 students from six comparison schools answered a computer-based questionnaire during class, representing 73 % and 81 % of eligible students, and 22 % of all technical/agricultural vocational schools in Denmark. Follow-up assessment was conducted 10 weeks after baseline and at the same time teachers of the intervention classes answered a questionnaire about implementation. School dropout rates will be tracked via national education registers through a 2-year follow-up period.

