## Methods

### Study design

Shaping the Social employed a non-randomised cluster controlled design with four intervention schools and six comparison schools. Comparison schools continued with their usual practice.

Intervention schools were selected by convenience sampling; the four schools involved in the development phase of the intervention agreed to become intervention schools. We chose this strategy in order to facilitate the implementation. The four intervention schools are located in major towns dispersed in Denmark and the schools are characterized as being large schools and offering a large range of technical or agricultural basic courses, for example carpenter and zookeeper. Characteristics of the intervention schools were used to select comparison schools among schools with the best match. However, a straight matched-pair design was not possible. Vocational schools in Denmark were ranked according to the following criteria: (1) at least one basic course offered for inclusion in the intervention group, (2) large school size (student population ≥ 800), (3) urban/suburban. Sixteen vocational schools were eligible. Subsequently, eight comparison schools were selected by geographic diversity. Letters explaining the study were sent to the school management, and schools expressing an interest (*n* = 7) were then visited individually. One school withdrew due to the time commitment entailed in the data collection. After selection of comparison schools, one intervention school wanted to include agricultural basic courses, which we accepted; however, the comparison schools were not selected on this criterion.

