### Setting

After nine compulsory years of primary and lower secondary school, almost all young people of Denmark choose to continue into the academically oriented upper secondary schools system, which is preparing students for tertiary education or into vocational education organized in separate schools spread out across large and medium sized cities. About 23% will choose vocational education [27]. Vocational education includes commercial, agricultural, technical, and social and healthcare programs leading to professions such as farmer, carpenter or web integrator. All programs are initiated by a school-based basic course lasting 20–25 weeks. The basic courses usually started four times a year and are flexible in duration depending on the student’s prior qualifications and ambitions. This means that some students within a class finish the basic course before others, and therefore a class is not a definite unit. Additionally, the high dropout rate implies that classes are merged during the basic course. We defined a class as students entering the same programme (e.g., carpenter) on the same date at the same address.

The vocational schools are organized into two levels. The upper level is the school with a management board. Next level is departments (e.g., construction) which are each headed by an inspector, one or more educational managers and an administration manager, and, typically, the departments have separate physical area and culture. In Shaping the Social, the upper analyze level will be these departments within schools (named college units).

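### The effect model stops at 32 college units although arm was assigned by school (4 vs 6), so any between-school variance makes the standard errors too small

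*Protocol article*

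**What the plan says.** **Assignment.** The abstract states that "schools were selected to either implement the intervention or continue with normal practice for comparison". Study design describes a "non-randomised cluster controlled design with four intervention schools and six comparison schools". Participant flow counts respondents in the same way, "2,329 students from four intervention schools and 3,371 students from six comparison schools", and no school is described as contributing to both arms. Arm is therefore a property of the school.

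**Organisation.** Setting describes two levels. Of the first it says: "The upper level is the school with a management board". Below it are departments, each with its own inspector and managers and, typically, its own premises and culture.

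**Analysis.** Setting then fixes the top of the model: "the upper analyze level will be these departments within schools (named college units"). Evaluation methods repeats this, with "students nested within classes in which the intervention was implemented, and classes nested within college units". Participant flow gives the counts: "we included 32 college units of 10 large and diverse technical and agricultural vocational schools".

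The article mentions no school random effect, school-level test or variance clustered by school. Sample size sets a two-sided 5% level and gives ICCs of 0.006 to 0.05, counting classes as the clusters.

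**The concern.** The top random level lies one step below the level at which arm was assigned. All college units of a school are in the same arm and share its board and its route into the study. The intervention schools had helped to develop the programme; the comparison schools were those whose management expressed interest and stayed in. The components are for use by school management as well as teachers (Intervention content). Some variation between schools beyond that between departments is therefore plausible.

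Such variation enters the arm contrast averaged over about 10 schools. The planned model absorbs it into the college-unit variance and averages it over 32 units. Confidence intervals become too narrow, and a chance difference between four and six schools can be reported as an effect on well-being, smoking or dropout.

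**Working it through.** **Inputs from the article.** 10 schools (4 vs 6); 32 college units; class ICC 0.05 (smoking and student solidarity); class size 20; 110 classes, read as per group; two-sided 5%. This reading fits the article's total: 2 × 110 × 20 = 4,400, and 4,400 × 1.2 = 5,280.

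**Assumptions.** 13 vs 19 units, spread as 4, 3, 3, 3 and 4, 3, 3, 3, 3, 3 over the schools; equal unit sizes; 4,400 students in 220 classes. The ICC of 0.05 is split into school (s), unit (u) and class (c = 0.05 − s − u), with residual 0.95. An unadjusted comparison of unit means stands in for the multilevel model.

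**Formulas.** Students per unit: 4,400/32 = 137.5. Classes per unit: 220/32 = 6.875.

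- Variance of a unit mean, excluding school: v = u + c/6.875 + 0.95/137.5.
- True variance of the arm difference: s(43/169 + 61/361) + v(1/13 + 1/19) = 0.4234s + 0.1296v. Here 43 and 61 are the sums of squared unit counts per school in each arm.
- Expected variance reported with units as the top level: 0.1296(v + 0.849s), where 0.849 = [(13 − 43/13) + (19 − 61/19)]/30.

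**One case in full (s = 0.005, u = 0.005, c = 0.04).** v = 0.005 + 0.00582 + 0.00691 = 0.01773. True variance = 0.002117 + 0.002297 = 0.004414. Reported variance = 0.1296 × 0.02197 = 0.002847. The ratio of true to reported standard error is √(0.004414/0.002847) = 1.24.

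**Range.** Type I error comes from simulation under no effect with at least 40,000 runs per row.

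| School ICC | Unit ICC | True/reported SE | Type I error, t(30) | Type I error, z |
|---|---|---|---|---|
| 0 | 0.01–0.02 | 1.00 | 5% | 6% |
| 0.001 | 0.01 | 1.05 | 6% | 7% |
| 0.002 | 0.02 | 1.07 | 6–7% | 8% |
| 0.0025 | 0.0075 | 1.13 | 8% | 9% |
| 0.005 | 0.015 | 1.18 | 9% | 11% |
| 0.005 | 0.005 | 1.24 | 11% | 13% |
| 0.01 | 0.02 | 1.28 | 12% | 14% |
| 0.01 | 0.01 | 1.35 | 14% | 16% |
| 0.0125 | 0 | 1.52 | about 20% | 21% |

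The first row recovers the planned 5% with a t test. A t test on the ten school means with 8 df gave about 5% in every row.

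At the article's ICC of 0.016 (dropout considerations), with 5,700 respondents, t(30) gave about 10% for school/unit/class 0.002/0.004/0.01 and about 14% for 0.005/0.005/0.006.

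**Power once schools are the clusters.** Take smoking at 41% vs 0.8 × 41% = 32.8%, with 3,371 and 2,329 respondents and school ICC ρ. The variance is 0.41 × 0.59/3371 × [1 + (3371/6 − 1)ρ] + 0.328 × 0.672/2329 × [1 + (2329/4 − 1)ρ]. At ρ = 0.01 this is 0.000474 + 0.000645 = 0.001119, so the noncentrality is 0.082/0.0334 = 2.45 and power on 8 df is 0.58. At ρ = 0.002, 0.005 and 0.02, power is 0.97, 0.81 and 0.36. These are upper bounds, because class and unit variance is left out.

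**The case against.** **Departments were chosen for a reason.** Setting says that they have their own heads and, typically, a separate area and culture. This stands as a reason for a unit level, and it suggests that most variance above the class lies between departments. It favours the upper rows of the table and counts against the last one. It does not show that school variance is zero, since the board and the route into the study are shared.

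**The size is unknown.** A reader might infer that type I error certainly exceeds 5%, or that it is about 20%. The article supports neither. It gives no school-level ICC; at zero the t test holds its level, and the 20% needs department variance to be nil. Part of the excess in the z column comes from the normal reference rather than the missing level, and the article does not say which reference will be used.

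**The model is only approximated.** The unit split is assumed. Adjustment for baseline differences, which the article foresees, could reduce school variance. Follow-up respondents would number about 3,100 (0.58 × 2,329 + 0.52 × 3,371) if the rates are shares of baseline respondents. These points move the figures but not their direction.

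**Ten schools are few, and non-random allocation is disclosed.** Few schools is a reason for small-sample inference; leaving the level out hides the variance. Selection bias is a separate limitation, and disclosing it does not address clustering by school.

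**An article condenses.** Details of estimation may be left to a fuller plan, but here the top level is stated twice.

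**Conclusion.** The concern holds in conditional form. The article fixes a model whose top level is below the level of assignment. If schools vary beyond their departments, standard errors for the arm effect on all three primary outcomes are too small and the 5% level is not kept. Under the stated assumptions the inflation is slight at a school ICC of 0.001–0.002 (6–7% with t) and clear at 0.005–0.01 (9–14%). It vanishes only at zero. The exact figures rest on the assumed unit split, the ICC split and the use of unit means; the structural point does not. It should be corrected before the results are reported: it touches every primary analysis, needs no new data, and the article says that analysis is still under way.

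**What to change.** - Add school as the top random level: students in classes, classes in college units, college units in schools.
- Test arm on between-school degrees of freedom, about 8. For continuous outcomes use Satterthwaite or Kenward-Roger. For smoking status and dropout, which are not continuous, use between-within degrees of freedom or a two-stage t test on school summaries.
- Report the school-summary analysis alongside in all cases. It matters most if the school variance is estimated at zero, since the mixed model then falls back to the present one.
- Treat a school-level permutation test (210 ways to choose 4 of 10 schools) as supportive at most, because schools were not randomised.
- State that inference on the arm effect rests on 10 schools.

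**Cost.** A change of wording and modest extra analysis work. The real price is wider confidence intervals and lower power than the class-based calculation implies. The selection bias disclosed under Study strengths and limitations remains.
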